(1:1) using a randomisation scheme generated using a computer-generated list. Random block sizes of two and four will be used to reduce the predictability of treatment allocation. Each site will be provided with 64 envelopes containing the group allocation. The clinical trials pharmacist will open the envelopes in a sequential manner when a participant is recruited. The pharmacist will then dispense the study medicines as stated in the envelope ([varenicline and NRT lozenges] or [varenicline and placebo lozenges]) and hand these to the RA along with the envelope. The RA will then hand the medicine to the participant and provide detailed counselling. Participants will not be told whether they are receiving NRT or placebo lozenges.

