## 4. Statistical Considerations

### 4.1 Sample Size

To show a difference of 15% in continuous abstinence between study arms (based on continuous abstinence rate of 23% in varenicline trials) at the 5% level of significance with 80% power, we will need 160 subjects per arm. i.e. 320 participants in total from the six hospitals, , 160 in each of the study arms. The primary analysis will be intention to treat (ITT) and lost to follow-up participants will be regarded as smokers.

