### 4.2 Data Analysis

Data will be stored in a suitable database (e.g. REDCap™, ACCESS™) and exported for analysis in Statistical Package for Social Sciences (SPSS) (version 23.0; IBM, Armonk, NY) and Stata (ver 15, StataCorp, College Station, TX). As recommended by the Russell Standard, all randomised patients will be accounted for in the intention to treat (ITT) analysis. Participants with missing outcomes at follow-up or whose self-reported abstinence was not biochemically validated will be considered as smokers. Sensitivity analyses using multiple imputation methods will also be carried out. Deceased participants will be excluded from

analyses. In a supportive analysis of the primary efficacy endpoint, an analysis will also be conducted on the per protocol set, which excludes patients with any major protocol deviations.

Logistic regression analyses will be used to examine the efficacy of intervention on the primary outcome, after testing homogeneity between hospitals using a random effects meta-analysis. In the event of heterogeneity, a more robust model incorporating clustering by hospital will be fitted. The effect of intervention on continuous abstinence at 6 months will be tested in pre-specified subgroups (per hospital, nicotine dependence, highly motivated versus moderately motivated smokers and men versus women) using models fitted for each subgroup containing main effects for intervention and subgroup and an interaction between them. Statistical significance will be considered at a two-sided p value of 0.05.

All randomised participants who take at least one dose of the treatment medications will be included in the safety analysis. A chi-squared test will be done to compare the frequency of treatment withdrawal between the treatment and comparator arms. The number of participants discontinuing treatment prematurely for any reason will be summarised by treatment group and by reasons for discontinuation.

The incidence of all suspected adverse events will be summarised by treatment group under the following categories: type, severity, action taken and outcome. Severity of adverse events will be reported using the CTEAE grading scale (v5.0). The causality of the adverse events will be determined using the Noranjo algorithm.

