#### Sample size

Continuous abstinence rates at 52 weeks in clinical trials of varenicline were 22.5% for varenicline and 8.3% for placebo. To demonstrate an absolute difference of 15% in prolonged abstinence rate between study arms (estimate based on abstinence rates in varenicline-NRT trials) 6 at the 5% level of significance with 80% power, 160 subjects per arm were needed. A total of 320 participants were recruited from the five hospitals, i.e., 64 subjects from each hospital, 32 each in varenicline monotherapy and varenicline + NRT lozenges arms.

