| 
*Employed: full-time, part-time or casual; Unemployed: student, unemployed, home-duties, disabled, unable to work, retired/pensioner
 
†Other reasons for hospital admission include: conditions of the skin and soft tissues, reproductive, lymphatic, endocrine, urinary or nervous systems
 
PHQ-9: Patient Health Questionnaire-9
 |  |  |  |

819

820 The effectiveness analyses will be by intention to treat (ITT) and participants lost to follow-  
821 up will be regarded as smokers. Deceased participants will be excluded from analyses.

822 Abstinence outcomes (primary and secondary) at 3, 6 and 12 months will be estimated in  
823 each treatment arm. Logistic regression models (unadjusted) will be used to examine the  
824 efficacy of intervention on the primary and secondary abstinence outcomes at each follow-  
825 up visit, after testing homogeneity between hospitals using a random effects meta-analysis.  
826 In the event of heterogeneity, generalised estimating equation models incorporating  
827 clustering by hospital will be fitted.

828

829

830  
831  
832  
833  
834  
835  
836  
837  
838  
839  
840  
841  
842  
843  
844

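### Allocation appears blocked by hospital, but the main efficacy model includes hospital only if a weak, undefined heterogeneity test is positive, and then through GEE on five or six clusters with no stated variance method; this costs power, not type I error

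*Combined protocol and SAP*

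**What the plan says.** - **Allocation.** Protocol 3.3 describes 1:1 randomisation from a computer-generated list in random blocks of two and four, and adds: "Each site will be provided with 64 envelopes containing the group allocation". Envelopes are opened in order. The SAP (Sample size) gives 64 participants per hospital, 32 in each arm.
- **Main model.** Protocol 4.2 and the SAP (Statistical Analyses, text before Table 2) both use logistic regression "after testing homogeneity between hospitals using a random effects meta-analysis". The SAP calls these models unadjusted. The note under its Table 2 says every analysis is adjusted for baseline HSI. Neither names hospital as a covariate.
- **Fallback.** SAP: "In the event of heterogeneity, generalised estimating equation models incorporating" clustering by hospital. Protocol 4.2 promises only a more robust model that allows for clustering. Neither gives a test threshold, working correlation, variance estimator or small-sample correction.
- **Subgroups.** Protocol 4.2 already plans a per-hospital subgroup model with main effects and an interaction.
- **Number of hospitals.** Protocol 3 and 4.1 and the SAP's aim say six. The SAP's Sample size section says "A total of 320 participants were recruited from the five hospitals".

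**The concern.** If patients are randomised in blocks within hospital, the natural analysis conditions on hospital. The reason is that abstinence levels may differ between hospitals. A random-effects meta-analysis of hospital results tests something else: whether the treatment effect differs. So the gatekeeper does not address the reason for adjusting, and with 53–64 patients per hospital it has little power even for its own question.

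The rule also lets the outcome data choose the primary model, with neither the trigger nor the fallback fully defined. The fallback treats five or six hospitals as the independent units, although patients are randomised individually. A sandwich variance built from so few clusters is unreliable. At stake are some power and a primary p-value that depends on choices still open when the data are seen.

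**Working it through.** **1. Inputs from the documents.** Protocol 4.1 sets the control rate ("based on continuous abstinence rate of 23% in varenicline trials") and seeks an absolute gain of 15 points with 80% power. Protocol 4.2 sets the test level: "Statistical significance will be considered at a two-sided p value of 0.05". So p₁ = 0.23, p₂ = 0.38, mean 0.305, z = 1.960 and 0.842.

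**2. The plan's own figure.** Without continuity correction:

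n = [1.960·√(2·0.305·0.695) + 0.842·√(0.23·0.77 + 0.38·0.62)]² / 0.15² = (1.276 + 0.541)² / 0.0225 ≈ 146.7.

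With correction: (146.7/4)·[1 + √(1 + 4/(146.7·0.15))]² ≈ 159.8, i.e. 160. The stated 160 per arm is reproduced. Uncorrected power at 160 per arm is 83.3%.

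**3. Is allocation by hospital?** 5 × 64 = 320, the planned total, whereas 6 × 64 = 384. Sequential envelopes at each site, small blocks and 32 per arm per hospital point strongly to site-blocked allocation. Neither document says so outright.

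**4. How weak is the screen?** With 32 per arm, the SE of one hospital's log odds ratio is √[1/(32·0.1771) + 1/(32·0.2356)] = √0.309 = 0.56. A between-hospital SD of 0.5 in the log odds ratio is smaller than that noise. In simulation, a Q test at the 5% level flags such an SD in 13–21% of trials. Other sets of runs gave 9–22%, depending on average effect, hospital spread and number of hospitals.

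**5. Simulated behaviour.** 20,000 trials per scenario (1,000 for exchangeable GEE, which supplies the model-based row and part of the uncorrected-sandwich range); about 320 patients in five or six hospitals, 1:1 within hospital. Assumed, because the documents give no figure: hospital SD 0–0.8 on the logit; Q screen at 5% or 10%. HSI was not modelled.

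Type I error, effect common to all hospitals:

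| Analysis | Type I error |
|---|---|
| Unadjusted logistic | 3.8–5.0% |
| Hospital-stratified (CMH or fixed effects) | 4.6–5.3% |
| Whole two-stage rule, uncorrected sandwich | about 3.7–4.8% |
| GEE, uncorrected sandwich, used in every trial | 15–17% (5 sites), 12–14% (6 sites) |
| GEE, uncorrected sandwich, flagged trials only | below 1% |
| GEE, model-based SE | 4.3–5.2% |
| GEE, k/(k−1) factor and t(k−1) reference | 4.7–5.6% |

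Power at 23% versus 38%, 160 per arm:

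| Hospital SD (logit) | Unadjusted | Stratified |
|---|---|---|
| 0 | 83% | 83% |
| 0.3 | 82% | 83% |
| 0.5 | 80% | 81–82% |
| 0.8 | 75% | 78% |

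**6. The GEE branch as the plan would reach it.** With a common effect, the screen flags about 2–8% of trials by chance. In those trials GEE with an uncorrected sandwich detects 23% versus 38% about 39–53% of the time, against 80–84% for the stratified test. The screen responds to between-hospital variation in the effect, and the sandwich SE is built from the same variation, so a positive screen selects trials with wide sandwich SEs.

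Rough cost of the switch: from 0.02 × (80 − 53) ≈ 0.5 to 0.08 × (84 − 39) = 3.6 points. Omitting hospital adds 0–3 points. The extremes need not coincide; direct simulation of the whole rule gives about 1–5 points.

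**7. Effect truly varying.** With a log-odds-ratio SD of 0.5 and no average effect, rejection for the average over a wider population of hospitals is about 9–12% for the two-stage rule and 12–14% for the stratified test.

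**The case against.** The case for leaving the plan alone is substantial.

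- **The unadjusted branch is valid.** Its mean SE is 0.99–1.04 times the true SE under a common effect. The 3-point power loss needs a hospital SD of 0.8. Around 23%, one SD either way is about 12% to 40% abstinence, and nothing in the documents supports so wide a spread. This stands: the likely cost on this branch is 0–1 points.
- **The 12–17% figure is not the plan.** A reader might infer that the GEE fallback inflates false positives. That rate applies only if an uncorrected sandwich is used in every trial. The SAP uses GEE only after a positive screen, where rejection under a common null effect is below 1%.
- **The variance estimator is unstated.** Model-based or small-sample-corrected errors hold close to 5% even when GEE is always used. This stands too: the SAP leaves the method open and does not prescribe a bad one.
- **Fixed hospital effects are no cure for effect heterogeneity.** Step 7 shows this, and it limits what the fix can claim.
- **Hospital is already in the subgroup model.** True, but that model is not the main efficacy analysis.

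The objection does not remove the undefined trigger, the undefined fallback, or the loss of power in flagged trials if a default robust variance is used.

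**Conclusion.** The point holds as a matter of efficiency and specification. The main efficacy model leaves out the factor by which patients appear to have been randomised, unless a low-power test of a different question is positive. What follows a positive test is not fully defined. The cost is about 1–5 points of power for the whole rule, assuming a common effect, a 5–10% screen and an uncorrected sandwich. If another variance method is used, the 39–53% detection figure does not apply, and on the unadjusted branch the loss is 0–1 points at hospital SDs up to 0.4–0.5 and about 3 at 0.8.

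Two stronger readings are not supported. A reader might conclude that standard errors are wrong whichever branch is taken. The unadjusted branch is in fact near nominal to mildly conservative, and the rule as a whole stays at about 3.7–4.8%. A reader might also take stratification by hospital as documented. It is a strong inference from the envelopes and the 32-per-arm figure, not a statement in either text.

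This is a free improvement. It does not invalidate the planned analysis, and the sample size of 160 per arm is not in error.

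**What to change.** 1. Delete the homogeneity pre-test and the switch to GEE from Protocol 4.2 and the SAP.
2. For the primary and every secondary abstinence outcome, fit one logistic model with arm, hospital (fixed effects) and baseline HSI. State that the odds ratio is conditional on hospital and HSI.
3. Report hospital-by-arm descriptively, as the subgroup interaction already planned.
4. State that hospital fixed effects deal with differences in abstinence level. They do not support inference to a wider population of hospitals if the effect truly varies.
5. If GEE is kept, specify the screen threshold, working correlation, variance estimator and small-sample correction.
6. State whether randomisation was stratified by hospital, and reconcile six hospitals with five.
7. Reconcile the SAP's unadjusted label with its HSI adjustment, and say which odds-ratio column of Table 2 is primary.

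Cost: SAP wording and four or five extra model terms. No new data are needed.

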**Table 2: Smoking abstinence rates by treatment groups from 2 weeks to 3, 6 and 12 months**

| Outcome                                         | Intervention
n (%) | Control
n (%) | P-value | Odds
ratio
(95%
CI) | Adjusted
odds ratio
(95%CI) |
|-------------------------------------------------|-----------------------|------------------|----------------|------------------------------|-----------------------------------|
| Smoking abstinence at 3-months           |                       |                  |                |                              |                                   |
| Self-reported prolonged abstinence              |                       |                  |                |                              |                                   |
| Self-reported 7-day point prevalence abstinence |                       |                  |                |                              |                                   |
| Smoking abstinence at 6-months           |                       |                  |                |                              |                                   |
| Biochemically verified prolonged abstinence     |                       |                  |                |                              |                                   |
| Self-reported prolonged abstinence              |                       |                  |                |                              |                                   |
| Self-reported 7-day point prevalence abstinence |                       |                  |                |                              |                                   |
| Smoking abstinence at 12-months          |                       |                  |                |                              |                                   |
| Biochemically verified prolonged abstinence     |                       |                  |                |                              |                                   |
| Self-reported prolonged abstinence              |                       |                  |                |                              |                                   |
| Self-reported 7-day point prevalence abstinence |                       |                  |                |                              |                                   |

Deceased participants at each time-point will be excluded from those specific analyses. All analyses will be adjusted for baseline HSI score.

HSI and PHQ-9 score differences from baseline to 3, 6 and 12 months will be compared between the treatment groups using Mann-Whitney U tests.

**Table 3: Heaviness of Smoking Index and Patient Health Questionnaire-9 score differences from baseline to 3, 6 and 12 months**

| Outcome          | Baseline     |         | 3-months     |         | 6-months     |         | 12-months    |         |
|------------------|--------------|---------|--------------|---------|--------------|---------|--------------|---------|
|                  | Intervention | Control | Intervention | Control | Intervention | Control | Intervention | Control |
| HSI score |              |         |              |         |              |         |              |         |
| HSI score | ----         | ----    |              |         |              |         |              |         |

|                                                   |      |      |  |  |  |  |  |  |
|---------------------------------------------------|------|------|--|--|--|--|--|--|
| (% participants showing improvement) † |      |      |  |  |  |  |  |  |
| PHQ-9 score                                       |      |      |  |  |  |  |  |  |
| PHQ-9 score (% participants showing improvement)  | ---- | ---- |  |  |  |  |  |  |

860 \*Indicates significant differences ( $p < 0.05$ ) between the intervention and control groups. †Follow-up score  
861 lower than baseline score indicates improvement

862  
863  
864  
865  
866  
867

868 A data safety and monitoring board (DSMB) provided oversight of adverse event data on a  
869 periodic basis. For the primary safety outcome, the proportion of reported adverse events  
870 occurring between treatment initiation and over 12-month follow-up will be compared  
871 between the treatment groups using a  $\chi^2$  test or Mann-Whitney U tests, as appropriate.

872 **Table 4: Adverse events experienced by treatment group**

| Outcome                                                              | Intervention | Control | P-value |
|----------------------------------------------------------------------|--------------|---------|----------------|
| Adverse events experienced at week 1 * , n (%)            |              |         |                |
| Adverse events experienced at week 1 * , Median and IQR   |              |         |                |
| Adverse events experienced at week 2 † , n (%)            |              |         |                |
| Adverse events experienced at week 2 † , Median and IQR   |              |         |                |
| Adverse events experienced at 3-months ‡ , n (%)          |              |         |                |
| Adverse events experienced at 3-months ‡ , Median and IQR |              |         |                |

|                                                                         |  |  |  |
|-------------------------------------------------------------------------|--|--|--|
| Adverse events experienced at 6-months § , n (%)             |  |  |  |
| Adverse events experienced at 6-months § , Median and IQR    |  |  |  |
| Adverse events experienced from week 2 to 6-months # , n (%) |  |  |  |

873

874

875 **Table 5: Adverse events experienced by treatment group at 1-week, 2-week, 3-months and 6-months**

| Adverse events                    | 1-week * |         | 2-week † |         | 3-months ‡ |         | 6-months § |         | Overall # |         |
|-----------------------------------|---------------------|---------|---------------------|---------|-----------------------|---------|-----------------------|---------|----------------------|---------|
|                                   | Intervention        | Control | Intervention        | Control | Intervention          | Control | Intervention          | Control | Intervention         | Control |
| Nausea                            |                     |         |                     |         |                       |         |                       |         |                      |         |
| Vomiting                          |                     |         |                     |         |                       |         |                       |         |                      |         |
| Indigestion                       |                     |         |                     |         |                       |         |                       |         |                      |         |
| Heartburn                         |                     |         |                     |         |                       |         |                       |         |                      |         |
| Irritation of the mouth or throat |                     |         |                     |         |                       |         |                       |         |                      |         |
| Constipation                      |                     |         |                     |         |                       |         |                       |         |                      |         |
| Weight gain                       |                     |         |                     |         |                       |         |                       |         |                      |         |
| Abdominal pain                    |                     |         |                     |         |                       |         |                       |         |                      |         |
| Increased appetite                |                     |         |                     |         |                       |         |                       |         |                      |         |
| Headaches                         |                     |         |                     |         |                       |         |                       |         |                      |         |
| Trouble sleeping at night         |                     |         |                     |         |                       |         |                       |         |                      |         |
| Abnormal dreams                   |                     |         |                     |         |                       |         |                       |         |                      |         |
| Mood swings                       |                     |         |                     |         |                       |         |                       |         |                      |         |
| Restlessness                      |                     |         |                     |         |                       |         |                       |         |                      |         |
| Dry mouth                         |                     |         |                     |         |                       |         |                       |         |                      |         |
| Thoughts of self-harm             |                     |         |                     |         |                       |         |                       |         |                      |         |
| Changes in mood or behaviour      |                     |         |                     |         |                       |         |                       |         |                      |         |
| Other**                           |                     |         |                     |         |                       |         |                       |         |                      |         |

\*\*Other includes: hiccups; dizziness; sweats; palpitations; rashes; metallic taste; etc.

**Per protocol analysis:** All randomized participants who took at least one dose of the treatment medications will be included in the per protocol analysis.

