### 3.9.1 Baseline Data

Information collected at the time of the baseline interview after obtaining written informed consent will include the following:

- Demographic information: contact details, country of birth, age, gender, education, employment status, living arrangement and possession of concession cards
- Smoking habit: age when they started, average number of cigarettes smoked per day, previous quitting experiences and methods used, perceptions about smoking cessation and willingness/confidence to quit

- Nicotine dependence: nicotine dependence will be assessed using the 2-item Heaviness of Smoking Index (HSI)
- Psychological distress: presence and extent of psychological distress will be assessed using the Patient Health Questionnaire (PHQ-9)
- Participant's motivation to quit smoking and confidence to quit smoking will be assessed using a 10 point scale with one being 'very low' and 10 being 'very high'
- Medical history: including a list of all current medications and medical conditions

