### 3.9.3 Secondary Outcome Measures

The secondary outcome measures are:

- Self-reported continuous abstinence from 2 weeks to three-, six- and twelve- months from treatment initiation
- CO verified continuous abstinence from 2 weeks to 12 months from treatment initiation for participants who self-report abstinence at this follow-up
- Self-reported 7-day point prevalence abstinence (i.e. smoking not even a puff in the past 7 days on the day of follow-up) measured from 2 weeks to 3, 6 and 12 months from treatment initiation
- CO verified 7-day point prevalence abstinence from 2 weeks to 6 and 12 months from treatment initiation for participants who self-report abstinence at these follow-ups
- Participant self-reports of withdrawal symptoms and cravings using the Mood and Physical Symptoms Scale (MPSS)
- Self-report of treatment adherence using the 8-item Tool for Adherence Behaviour Screening (TABS)
- Adverse events experienced from study medications
- Change in psychological distress
- Number of Quitline sessions attended/received
- Other health resources used including emergency department visits, GP visits (for smoking cessation), over-the-counter medicines used as well as the use of other smoking cessation therapies and alternate products

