| Moderately severe depression (score 15-19)                                                                                                                                                                                                                                                                                                                    |  |  |  |
| Severe depression (score 20-27)                                                                                                                                                                                                                                                                                                                               |  |  |  |
| Reason for hospital admission                                                                                                                                                                                                                                                                                                                          |  |  |  |
| Cardiovascular disorder                                                                                                                                                                                                                                                                                                                                       |  |  |  |
| Respiratory disorder                                                                                                                                                                                                                                                                                                                                          |  |  |  |
| Digestive system disorder                                                                                                                                                                                                                                                                                                                                     |  |  |  |

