| Moderate nicotine dependence (score 3-4)                                                                                                                                                                                                                                                                                                                      |  |  |  |
| High nicotine dependence (score 5-6)                                                                                                                                                                                                                                                                                                                          |  |  |  |
| Motivation to quit, median [IQR]                                                                                                                                                                                                                                                                                                                       |  |  |  |
| Confidence to quit, median [IQR]                                                                                                                                                                                                                                                                                                                       |  |  |  |
| Tried quitting at least once in the last 12 months, n (%)                                                                                                                                                                                                                                                                                              |  |  |  |
| Number of quit attempts in the last 12 months, median [IQR]                                                                                                                                                                                                                                                                                            |  |  |  |

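### HSI and PHQ-9 change scores are compared by Mann-Whitney tests with no baseline covariate and no planned between-arm estimate or interval; a baseline-adjusted model would be a free gain

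*Combined protocol and SAP*

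**What the plan says.** Protocol 3.9.1 collects both scales at baseline: HSI for nicotine dependence and PHQ-9 for psychological distress. Protocol 3.9.3 lists "Change in psychological distress" as a secondary outcome. Change in HSI is not in that list.

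The SAP (Statistical Analyses, between Tables 2 and 3) says: "HSI and PHQ-9 score differences from baseline to 3, 6 and 12 months will be compared between the treatment groups using Mann-Whitney U tests". For each arm and visit, Table 3 then shows the score and the percentage of "participants showing improvement", with an asterisk where p<0.05. It has no column for a difference between arms or for a confidence interval. SAP Tables 2 and 6, for abstinence, do give odds ratios with 95% CIs.

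Just before the Mann-Whitney sentence, following Table 2, the SAP says: "All analyses will be adjusted for baseline HSI score". The text before Table 2 calls the logistic models for abstinence unadjusted, while Table 2 itself has an adjusted odds ratio column.

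**The concern.** In a randomised comparison, a baseline measurement of the outcome is most useful as a covariate, with its coefficient estimated from the data. A change score sets that coefficient to 1. Unless the true regression slope of follow-up on baseline is 1, this adds noise to the treatment comparison.

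Psychological distress is a stated secondary outcome. With Table 3 as planned, a missing asterisk would not show what difference between arms the data exclude. A less efficient test also makes a missing asterisk more likely when a difference exists.

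**Working it through.** **Inputs from the documents.** Both scores are measured at baseline (protocol 3.9.1). The top category ends at 6 for HSI and 27 for PHQ-9 (SAP Table 1). Allocation is 1:1 (protocol 3.3), with 160 per arm (4.1) and two-sided 0.05 (4.2).

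**Assumed, because the documents do not give them.** The baseline/follow-up correlation r, the ratio k of follow-up SD to baseline SD, and the size of any treatment effect.

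**The plan's own figure.** No sample size or power is stated for HSI or PHQ-9. The 160 per arm belongs to abstinence and reproduces there: 23% versus 38%, two-sided 0.05 and 80% power give 147 per arm without and 160 with continuity correction. It is used below only as the number per arm.

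**Step 1: variance.** Take baseline SD = 1 and follow-up SD = k.
- Change score: 1 + k² − 2rk
- Baseline-adjusted (ANCOVA): k²(1 − r²)
- Change minus ANCOVA: (1 − rk)², which is never negative

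So the adjusted analysis is never less precise in large samples. The two are equal only when the slope rk is 1. With k = 1 the ratio is (1 − r²)/(2(1 − r)) = (1 + r)/2.

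| r | k = 1 | k = 1.25 | k = 1.5 |
|---|---|---|---|
| 0.3 | 0.91/1.40 = 0.65 | 1.422/1.813 = 0.78 | 2.048/2.350 = 0.87 |
| 0.5 | 0.75/1.00 = 0.75 | 1.172/1.313 = 0.89 | 1.688/1.750 = 0.96 |
| 0.7 | 0.51/0.60 = 0.85 | 0.797/0.813 = 0.98 | 1.148/1.150 = 1.00 |

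If the follow-up SD is smaller than baseline, the ratio falls below the k = 1 column and the gain is larger. With k = 1 and r below 0.5, the change score (variance 2(1 − r) > 1) is also less precise than the follow-up score alone.

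**Step 2: power.** Suppose ANCOVA has 80% power. A change-score comparison of means then has power Φ((1.96 + 0.84)√ratio − 1.96).
- k = 1: 62%, 68% and 73% at r = 0.3, 0.5 and 0.7. To match ANCOVA with 160 per arm, the change score needs 160/0.65 = 246, 160/0.75 = 213 and 160/0.85 = 188 per arm.
- k = 1.25: about 70%, 75% and 79%.

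**Step 3: does this carry over to a rank test on bounded scores?** The formulas above concern means, so the methods were also simulated with 160 per arm, an assumed shift of 0.3 SD on the underlying scale and 3,000 runs per setting for power.

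| Score | r (underlying) | Mann-Whitney on change | ANCOVA | Rank ANCOVA |
|---|---|---|---|---|
| Skewed 0–27 | 0.3 | 55% | 75% | 78% |
| | 0.5 | 67% | 82% | 85% |
| | 0.7 | 86% | 92% | 94% |
| 0–6 | 0.3 | 58% | 79% | 77% |
| | 0.5 | 71% | 85% | 83% |
| | 0.7 | 88% | 94% | 92% |

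Type I error was 4% to 6% for all three methods. Skewed or bounded scores therefore do not favour the planned test, and it is not invalid.

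**Step 4: the HSI-adjustment sentence.** There are two readings.
- It is a note to Table 2. This is the likelier one: it follows a sentence on deceased participants that recurs under Table 6, where there is no adjusted column and no adjustment sentence. HSI and PHQ-9 changes then have no covariate adjustment.
- It covers every analysis. The SAP then asks for something a Mann-Whitney test cannot do, and for PHQ-9 it names a different scale's baseline.

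**The case against.** The best defence is that the protocol defines the outcome as a change, so testing change matches the endpoint, and that randomisation keeps the comparison unbiased. Both points stand. Neither favours the planned test: in a linear model with baseline as covariate, the treatment coefficient is the same whether the response is the follow-up score or the change.

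The size of the gain is also open to challenge, and rightly. Equal SDs are doubtful for HSI. Entry requires at least 10 cigarettes a day (protocol 3.1), which narrows baseline, while quitting may widen follow-up. The k = 1.25 and 1.5 columns show how far the gain could then shrink.

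A reader might infer stronger points that the documents do not support:
- *The baseline is ignored.* It is subtracted; only its coefficient is not estimated.
- *No effect size is possible.* Crude differences follow from Table 3, and a Hodges-Lehmann shift with its interval can accompany a Mann-Whitney test. The SAP simply plans neither.
- *The HSI test compares only continuing smokers.* The documents do not say how abstainers are scored, so this is conjecture.
- *The scales are not collected at 3 and 6 months.* Protocol 3.8.3 and 3.8.4 do not list them, but SAP Table 3 has columns for those visits. This is missing detail and does not show that the data are absent.
- *A safety endpoint is left unprotected.* PHQ-9 is not named as one. Mood-related adverse events are tabulated separately in SAP Table 5, with DSMB oversight.

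**Conclusion.** The point holds as one of efficiency and reporting. The planned test is valid, the scales are not primary endpoints, and no primary conclusion depends on them.

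The direction is firm: baseline adjustment cannot lose precision in large samples and gains unless the slope is 1. The size is not firm. The variance ratio runs from 0.65 to 0.85 with equal SDs and from 0.78 to 0.98 with a follow-up SD 1.25 times baseline, over assumed r of 0.3 to 0.7. At 1.5 times and r = 0.7 the gain all but disappears. The missing between-arm estimate and interval does not depend on any of these assumptions. The HSI-adjustment sentence cures neither part on either reading.

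**What to change.** In the SAP:
- Replace the Mann-Whitney tests with a model of each follow-up score on treatment and that score's own baseline: proportional-odds regression, or ANCOVA with robust standard errors. Name one of them in advance.
- Add to Table 3 the adjusted between-arm effect (odds ratio or mean difference) with 95% CI at 3, 6 and 12 months.
- State whether the HSI-adjustment sentence applies only to Table 2.

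If the sponsor prefers to keep the Mann-Whitney test, a Hodges-Lehmann estimate with its interval would supply the missing estimate but not the precision.

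The cost is a few lines of SAP text, an added Table 3 column and a little code, with no new data. The change should be dated before these scores are examined by arm.
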